### 2.4. Standard Smoking Cessation Program (Control Protocol)

A tailored, multimodal behavioral smoking cessation rehabilitation program delivered exclusively through in-person care will be used for the CG. The behavioral and psychological interventions provided to the CG will be equivalent to those delivered to the EG (described in Section 2.3), differing only in the mode of delivery, namely, face-to-face assistance rather than telemedicine-based rehabilitation.

The behavioral and psychological interventions will be provided during follow-up visits in order to address behavioral difficulties, maintain motivation, and support long-term abstinence.

For home monitoring of cardiopulmonary parameters, portable medical devices already available in participants’ possession, such as sphygmomanometers and pulse oximeters, will be used to manually record heart rate, blood pressure, respiratory rate, and oxygen saturation twice a day for up to 12 months. Unlike the EG, physiological parameters in the CG will not be automatically transmitted to a telemedicine platform, and no wearable remote-monitoring devices will be used. No participant will be required to independently purchase portable medical devices in order to participate in the study, according to the aforementioned exclusion criteria for the CG.

Similar to the EG, participants allocated to the CG will complete a paper-based smoker diary developed by the Italian Ministry of Health and the National Institute of Public Health (freely available on https://smettodifumare.iss.it/documents/d/guest/guida-smetto-di-fumare-a5-v07, accessed on 12 May 2026), recording the daily number and frequency of cigarettes or nicotine-containing products used.

Participants in the CG will also self-report oral health-related parameters, including gingival bleeding during daily oral hygiene procedures performed at least twice a day throughout the rehabilitation program.

Healthcare providers involved in the multidisciplinary smoking cessation program, including dental, cardiologic, pneumological, and psychological specialists, will monitor participants exclusively through scheduled in-person visits according to the rehabilitation program and participants’ clinical needs. Additional in-person specialist evaluations may be scheduled whenever considered clinically necessary.

### 2.5. Outcomes and Data Collection

#### 2.5.1. Primary Outcome

The primary outcome of the study will be the effectiveness of the program on smoking cessation, assessed through Continuous Abstinence Rates (CARs) and Point Prevalence Abstinence (PPA).

CARs will be defined as sustained smoking abstinence throughout the follow-up period without relapse [28]. CARs will be calculated as the proportion of participants who maintain continuous smoking abstinence at the 6-month and 12-month follow-up assessments without relapse during the observation period.

PPA will be defined as abstinence from smoking at the time of assessment, regardless of any previous smoking relapses during follow-up [28]. PPA will be calculated as the proportion of participants reporting abstinence from smoking at the 6-month and 12-month follow-up assessments, regardless of previous smoking relapses during follow-up.

Both CARs and PPA will be assessed using self-reported smoking status collected through the smoker diary and will be computed 6 and 12 months after baseline [28]. Smoking abstinence outcomes will be assessed through self-reported smoking status, consistent with the telemedicine-based design of the Wear-Smile project.

No biochemical verification of smoking abstinence (e.g., exhaled carbon monoxide or cotinine testing) will be performed.

The timing at 6 and 12 months to assess smoking behavior status was established because a 6-month abstinence period was considered indicative of long-term smoking cessation, as it allows for a more reliable estimation of the proportion of participants who will maintain abstinence even in the subsequent years [8]. A permanent effect of smoking cessation treatment was estimated to be 50% of the Continuous Abstinence Rate at 6 months [8].

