## Abstract

Background: Tobacco smoking remains one of the leading preventable causes of morbidity and mortality worldwide and is associated with cardiovascular, respiratory, oral, and psychological disorders. Although conventional smoking cessation interventions are effective, barriers related to accessibility, adherence, healthcare costs, and continuity of care frequently limit long-term success. Recent advances in technology may offer innovative opportunities to improve multidisciplinary smoking cessation pathways. Methodology: The Wear-Smile project is a non-profit, monocentric, randomized controlled trial registered in the Clinical Trial Protocol Registry and Results System (code No.: NCT07593742), designed to evaluate the effectiveness of a multidisciplinary telemedicine-based smoking cessation program assisted by wearable remote-monitoring devices. Adults who smoke combustible or heated tobacco or electronic nicotine delivery systems will be randomly allocated in a 1:1 ratio to either an experimental group receiving telemedicine-assisted rehabilitation integrated with wearable monitoring devices or a control group receiving standard in-person smoking cessation care. The intervention will include a multidisciplinary behavioral smoking cessation intervention involving cardiology, respiratory, dental, and psychology specialists. Primary outcomes will include Continuous Abstinence Rates and Point Prevalence Abstinence assessed at 6 and 12 months. Secondary outcomes will include cardiopulmonary and oral health parameters, smoking-related variables, health- and oral health-related quality of life (QoL), as well as adherence, usability, acceptability, and satisfaction with the rehabilitation program. Conclusions: The project may provide preliminary evidence regarding the potential feasibility, acceptability, and effectiveness of a multidisciplinary smoking cessation program integrating telemedicine and wearable monitoring technologies in improving abstinence outcomes, patient engagement, continuity of care, and QoL.

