### 2.6. Statistical Analysis

An a priori sample size estimation was performed using G*Power software version 3.1.9.7 [36]. The calculation was based on the primary outcome (CAR), assuming a one-tailed test, a type I error (α) of 0.05, a statistical power (1−β) of 0.80, and a medium expected effect size. Based on these assumptions, the estimated sample size is 102 participants (51 per group).

The data collected will be pseudonymized (a technique that modifies and masks personal and sensitive data of a natural person to prevent direct or easy attribution to the individual) and will be used exclusively for the purposes of the Wear-Smile study project.

Statistical analyses will be performed according to the intention-to-treat (ITT) principle. Per-protocol analyses will additionally be conducted as sensitivity analyses.

The statistical analysis will be applied to analyze continuous and categorical variables, with particular attention to the handling of missing data and the analysis of both intra- and inter-subject variability.

To enhance data interpretation and understanding of distributions, graphical representations such as histograms, boxplots conditioned on the target variable, and scatter plots will be employed.

To minimize the risk of bias due to missing data, a missing data analysis will be performed to assess whether data are Missing Completely at Random (MCAR) or dependent on other variables. If missing data exceeds 5%, it will be handled using multiple imputation techniques based on appropriate statistical models, thereby reducing the risk of bias.

The adoption of these methodologies will strengthen the scientific evidence regarding the effectiveness of telerehabilitation for smoking cessation, optimize result interpretation, and provide valuable insights for future clinical implementations and public health policies.

A sensitivity analysis will be conducted to compare results between the original datasets and the imputed datasets.

Statistical analyses will be performed using SPSS version 28.0, R version 4.2, or STATA version 17.0. The level of statistical significance will be set at *p* < 0.05 for all tests, with Bonferroni correction applied for multiple comparisons to control the risk of Type I error. Effect sizes and 95% confidence intervals (95% CI) will also be reported whenever appropriate.

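### Four unranked primary results (CAR and PPA at 6 and 12 months), but a sample size for one unadjusted test that ignores the plan's own Bonferroni correction

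*Protocol article*

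**What the plan says.** Section 2.5.1 of the protocol article gives the primary outcome as effectiveness on smoking cessation, "assessed through Continuous Abstinence Rates (CARs) and Point Prevalence Abstinence (PPA". Both measures "will be computed 6 and 12 months after baseline". The Abstract lists the same set in the plural: "Primary outcomes will include Continuous Abstinence Rates and Point Prevalence Abstinence assessed at 6 and 12 months". Neither place ranks the measures, names a deciding time point, or says whether one, any or all of the results must be significant.

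Section 2.6 treats the primary outcome as a single quantity: "The calculation was based on the primary outcome (CAR", with no month attached. The remaining sizing inputs are "assuming a one-tailed test, a type I error (α) of 0.05", "a statistical power (1−β) of 0.80" and "a medium expected effect size", which lead to 102 participants, 51 per group.

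The same section sets p < 0.05 for all tests, "with Bonferroni correction applied for multiple comparisons to control the risk of Type I error". It does not say which comparisons form the family or what the divisor is. Abstinence is to be compared by Chi-square or Fisher's exact test, with no sidedness stated. Section 2.7 reports that enrolment has not begun.

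**The concern.** The article fixes three things that do not fit together: four primary results, a sample size for one test at full alpha, and a Bonferroni correction. The primary outcome is CAR and PPA in the Abstract and Section 2.5.1, but CAR alone in the sizing paragraph.

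The four results also overlap by definition. Abstinence sustained to month 12 implies abstinence sustained to month 6, and anyone continuously abstinent at a visit also counts as point-prevalence abstinent at that visit. Bonferroni makes no use of this overlap and is conservative for such a set.

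Two things are at stake. Without a success rule, the same data could be called positive or negative depending on which result is put forward. And if the stated correction is applied to the four, the stated 80% power does not hold for any one of them.

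**Working it through.** **Inputs from Section 2.6:** one-tailed alpha 0.05, power 0.80, medium effect, 51 per arm. **Assumptions:** medium means d = 0.5 (or h = 0.5 for proportions), since no figure or abstinence rate is given; Bonferroni covers exactly the four primary results, so alpha per test is 0.05/4 = 0.0125.

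**Step 1: reproduce the 102.** Normal approximation, n per arm = 2(z₁₋α + z₁₋β)²/d² = 2(1.645 + 0.842)²/0.25 = 49.5, so 50. The exact two-sample t-test gives 51 per arm, 102 in total, with power 0.806. That matches the article and contains no multiplicity allowance. Two variants do not match: a two-sided t-test needs 64 per arm (128), and a Chi-square test with w = 0.3 needs 88 in total.

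**Step 2: power per endpoint at 51 per arm.** Noncentrality = d√(n/2) = 0.5 × √25.5 = 2.525. Normal approximation to power = Φ(2.525 − z).

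| Test | z | Φ(2.525 − z) | Exact t |
|---|---|---|---|
| one-sided 0.05 | 1.645 | 0.81 | 0.81 |
| two-sided 0.05 | 1.960 | 0.71 | 0.71 |
| one-sided 0.0125 | 2.241 | 0.61 | 0.60 |
| two-sided 0.0125 | 2.498 | 0.51 | 0.50 |

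Under the article's own one-tailed test, Bonferroni alone takes power from 0.81 to 0.60. The 0.50 also includes the move to two-sided testing.

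**Step 3: check on the proportion scale.** With h = 0.5 and assumed control rates of 5% to 30%, power per endpoint at 0.0125 is 0.56 to 0.60 one-sided and 0.46 to 0.50 two-sided. Exact enumeration at 0.0125 gives 0.47 to 0.50 for the two-sided Chi-square, 0.36 to 0.42 for two-sided Fisher and 0.47 to 0.53 for one-sided Fisher.

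**Step 4: power for the whole set under Bonferroni.** Simulated normal test statistics, equal effects d = 0.5 on all four, common pairwise correlation assumed 0.5 to 0.9:

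| Success rule | One-sided | Two-sided |
|---|---|---|
| at least one of four | 0.88 to 0.73 | 0.81 to 0.64 |
| all four, each at 0.0125 | 0.31 to 0.48 | 0.21 to 0.38 |

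(First figure at correlation 0.5, second at 0.9.)

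**Step 5: familywise error in the same model.** With Bonferroni it is 0.041 to 0.025 one-sided and 0.043 to 0.026 two-sided. If any of the four at an unadjusted 0.05 counted as success, it would be 0.144 to 0.087 one-sided and 0.156 to 0.094 two-sided.

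**Step 6: size needed for 80% per endpoint at 0.0125.** Normal formula: one-sided 8 × (2.241 + 0.842)² = 76.0, so 77; two-sided 8 × (2.498 + 0.842)² = 89.2, so 90. The exact t-test gives 78 per arm (156) and 91 per arm (182), before dropout.

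**The case against.** The strongest reply has four parts.

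- **Section 2.6 calls CAR the primary outcome, so a lead measure is implied.** This stands in part. It still gives no month, and it conflicts with Section 2.5.1 and the Abstract.
- **The Bonferroni family and the testing order are details that an analysis plan usually settles.** This is fair for the divisor, which is why 4 is only an assumption here. It does not cover the conflict between three rules that the article itself states.
- **Type I error is controlled.** If Bonferroni covers the primaries, this is right: familywise error stays below 5%, and mild conservatism is a matter of efficiency. A reader might infer that success on any of four tests at 0.05 is allowed, with familywise error roughly two to three times nominal. The documents do not support that, because it would depart from the stated correction.
- **The power loss can be overstated.** A reader might infer that Bonferroni by itself halves power, or that detecting the planned effect becomes a coin-flip. Neither follows. The 0.50 is for one chosen endpoint and also includes a change of sidedness that the sizing does not make. The chance that at least one of four passes is considerably higher.

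The preference for 6 months is also open to debate. Section 2.5.1 gives its rationale for the two time points together and does not rank them.

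**Conclusion.** The point holds as an inconsistency between stated rules. There are four overlapping primary results with no order or success rule, and the sample size allows nothing for the correction prescribed alongside it. The 102 participants give 0.81 power for one unadjusted one-sided test. With Bonferroni over four, they give about 0.60 per endpoint one-sided or 0.50 two-sided. Power for the set runs from 0.21 (all four must pass, two-sided) to 0.88 (any one, one-sided), so the missing success rule matters as much as the divisor.

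These figures rest on d = 0.5, a divisor of 4, no dropout and, for the set, equal effects with correlations of 0.5 to 0.9.

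**What to change.** Before the first participant is enrolled:

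1. Name one primary endpoint and time point. CAR at 6 months is a natural choice: CAR is the sizing outcome, and Section 2.5.1 gives a reason for 6 months. Another choice is valid if it is fixed now.
2. Test that endpoint at full alpha. Test the other three in a stated fixed order, each only if the one before succeeds, or make them secondary. State that Bonferroni does not apply to this sequence.
3. Use the same sidedness in sizing and analysis, and restate the power at 51 per arm: 0.81 at one-sided 0.05, or 0.71 at two-sided 0.05. Keeping 80% with two-sided testing would need 128 participants.
4. If four co-equal primaries with Bonferroni are kept instead, state the success rule and the divisor. Restate power per endpoint as about 0.60 one-sided or 0.50 two-sided, or enlarge the trial to about 156 or 182.
5. Bring the Abstract, Sections 2.5.1 and 2.6 and the registry entry into line.

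With the sample unchanged, the cost is wording and a registry update. The fixed order has a price: a later endpoint cannot be claimed once an earlier one fails. Two-sided testing at 51 per arm means accepting power below the stated 0.80.

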Specialist-specific contributions are as follows:Cardiologists: optimization of cardiovascular risk factors, therapeutic management, motivational support for smoking cessation, and counseling on the cardiovascular benefits of quitting smoking.Respirologists: assessment and management of respiratory comorbidities, pulmonary function evaluation, support for smoking-related respiratory issues, and counseling on the respiratory benefits of quitting smoking.Dentists: evaluation of oral health, management of smoking-related periodontal disease, and counseling on the oral benefits of quitting smoking.Psychologists: structured behavioral counseling, motivational interviewing techniques, management of psychological dependence, and emotional support.

All sessions are documented in the electronic health record to ensure traceability, reproducibility, and consistency between the two study arms.

On a voluntary basis, participants allocated to the study group will be asked to use the wearable remote-monitoring devices and record physiological parameters twice a day, for a maximum duration of the study of 12 months.

Following enrollment, the EG will receive training on the use of the integrated telemedicine platform and the wearable monitoring devices after the calibration of the devices.

The wearable devices will record participants’ cardiopulmonary parameters (heart rate, blood pressure, respiratory rate, and oxygen saturation) on the integrated telemedicine platform. In this way, the participant’s medical parameters will be automatically recorded through the wearable device and automatically transferred to the telemedicine platform.

Participants will also complete a paper-based smoker diary developed by the Italian Ministry of Health and the National Institute of Public Health (freely available on https://smettodifumare.iss.it/documents/d/guest/guida-smetto-di-fumare-a5-v07, accessed on 12 May 2026), recording the daily number and frequency of cigarettes or nicotine-containing products used.

Adherence to wearable device utilization will be automatically tracked through the telemedicine platform by recording the timing and frequency of device use.

Participants in the EG will also self-report oral health-related parameters, including gingival bleeding during daily oral hygiene procedures performed at least twice a day throughout the rehabilitation program.

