All detected smoking events and recorded parameters will be automatically transmitted to the telemedicine platform. In this way, the smoker’s diary will be automatically compiled through the wearable device recordings.

Finally, the integrated telemedicine platform and remote wearable monitoring devices will send push notifications to remind patients to take prescribed medications (particularly for fragile patients and those with comorbidities) at scheduled times.

The telemedicine platform and wearable devices will also periodically send text messages, photos, and videos to support smoking cessation.

Healthcare providers involved in the multidisciplinary smoking cessation program, including dental, cardiologic, pneumological, and psychological specialists, will be able to remotely monitor participants throughout the telerehabilitation program. When clinically necessary, treatment modifications may be proposed and shared among specialists and participants.

At any time, the patient will be able to request and schedule teleconsultation sessions via videoconference with the selected healthcare specialist through the integrated telemedicine platform, and vice versa. An in-person clinical evaluation should be scheduled if deemed necessary by the clinician.

The integrated telemedicine platform and wearable monitoring system will comply with applicable data privacy and security regulations.

Both the integrated telemedicine platform and wearable remote-monitoring devices will ensure compliance with data privacy and protection standards.

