#### 2.5.2. Secondary Outcomes

Secondary outcomes will include the longitudinal assessment of cardiopulmonary parameters, oral health conditions, smoking-related outcomes, health-related quality of life, oral health-related quality of life, and participants’ adherence, usability, acceptability, and patient and healthcare satisfaction with the rehabilitation program.

Cardiopulmonary parameters will include heart rate (beats per minute, bpm), blood pressure (mmHg), respiratory rate (breaths per minute), and oxygen saturation (SpO_2_, %). Heart rate, blood pressure, respiratory rate, and oxygen saturation will be measured twice daily throughout the 12-month study period. In the EG, these parameters will be automatically recorded twice daily through wearable remote-monitoring devices and transmitted to the integrated telemedicine platform. In the CG, the same parameters will be manually self-recorded twice daily using portable medical devices (sphygmomanometers and pulse oximeters) already available in participants’ possession. In addition, in-person clinical cardiology follow-up evaluations will be performed at baseline, 6 months, and 12 months by cardiology specialists for both EG and CG.Oral health outcomes will include probing depth (PD, mm) [29], full-mouth bleeding index (FMBI, percentage of bleeding sites) [30], and full-mouth plaque index (FMPI, percentage of plaque-positive sites) [31]. These clinical periodontal parameters will be assessed by calibrated dental specialists during standardized in-person periodontal examinations at baseline, 6 months, and 12 months. Periodontal examinations will be performed using a manual UNC-15 periodontal probe, and the periodontal parameters will be measured at six sites per tooth.

In addition, self-reported gingival bleeding during toothbrushing will be self-reported twice daily throughout the study period.

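### CAR and PPA are read only from a smoker diary, so an attender whose diary has lapsed has no primary outcome, and the article contradicts itself on how the experimental arm's diary is filled

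*Protocol article*

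**What the plan says.** - **Source of the primary outcome.** Section 2.5.1: "Both CARs and PPA will be assessed using self-reported smoking status collected through the smoker diary". The same section adds: "No biochemical verification of smoking abstinence (e.g., exhaled carbon monoxide or cotinine testing) will be performed". Table 1 schedules CAR and PPA at 6 and 12 months and names no other source.
- **How the diary is kept.** For the experimental group (EG), section 2.3 first says: "Participants will also complete a paper-based smoker diary developed by the Italian Ministry of Health". A few paragraphs later it says: "the smoker’s diary will be automatically compiled through the wearable device recordings". For the control group (CG), section 2.4 says: "Similar to the EG, participants allocated to the CG will complete a paper-based smoker diary". Section 2.5.2 also calls the diary paper-based, without distinction by arm.
- **Contact during the programme.** In the EG, providers "will be able to remotely monitor participants throughout the telerehabilitation program", and either side can start a teleconsultation. In the CG, providers "will monitor participants exclusively through scheduled in-person visits".
- **Existing contact at the primary time points.** Section 2.5.2: "in-person clinical cardiology follow-up evaluations will be performed at baseline, 6 months, and 12 months by cardiology specialists for both EG and CG". Periodontal examinations and all questionnaires fall at the same times.
- **Analysis.** Section 2.6 plans intention-to-treat (ITT) analysis, multiple imputation when more than 5% of data are missing, and a comparison of original with imputed data. The Discussion acknowledges reporting bias, attrition bias and differential engagement.

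**The concern.** An ITT comparison of abstinence needs smoking status at 6 and 12 months from everyone randomised, whether or not they still follow the programme. The article ties that status to an instrument that can stop being filled in while the participant keeps attending.

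A blank diary is also ambiguous. The writer may have quit and have nothing left to record, or may have relapsed and given up on the diary. Missing entries may therefore depend on smoking status, in either direction. PPA is by definition status on the day of assessment and does not need a year of daily entries at all.

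If, in addition, one arm's diary is filled by a device and the other's by hand, the primary endpoint is measured by two different methods in an unblinded trial. A difference in capture could then be read as a difference in abstinence.

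**Working it through.** **1. Is there a second source?** Section 2.5.1 gives the diary as the source for both measures, excludes biochemical checks and says that status is self-reported. No section names a direct smoking-status question at 6 or 12 months as the source of CAR or PPA. An attender without a diary thus has no endpoint under the text as written.

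**2. Is the diary the same in both arms?** Paper in the CG (2.4). Paper in general (2.5.2). In the EG, both paper and compiled by the wearable (2.3). The last two cannot both hold. Automatic compilation also sits badly with the self-report basis in 2.5.1 and with device use in the EG being voluntary (2.3): someone not using the device would leave a record that cannot be told apart from abstinence. Section 2.3.2 lists four cardiopulmonary measurements and does not say how a smoking event is derived from them.

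**3. The plan's own figure.** A one-sided two-sample t test with d = 0.5, alpha 0.05 and power 0.80 needs 51 per arm (power 0.806; 50 per arm gives 0.799). This matches the stated 102. It is used below only for the arm size.

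**4. Size without assumptions.** One missing outcome leaves 1/51 = 2.0 percentage points of that arm's rate undetermined. The 5% threshold for imputation is 0.05 × 102 = 5.1, so six missing outcomes pass it.

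**5. Illustration of bias.** The article gives no abstinence or loss rates, so these are assumptions: true abstinence 20% in both arms; loss 15% in the EG and 30% in the CG (about 8 and 15 of 51); q = proportion abstinent among those lost.

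- Complete-case rate = (0.20 - loss × q)/(1 - loss)
- Missing-as-smoking rate = 0.20 - loss × q

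| q | Rule | EG | CG | EG - CG (points) |
|---|---|---|---|---|
| 0.05 | complete case | 0.1925/0.85 = 22.6% | 0.185/0.70 = 26.4% | -3.8 |
| 0.05 | missing as smoking | 19.25% | 18.5% | +0.8 |
| 0.20 | complete case | 0.17/0.85 = 20.0% | 0.14/0.70 = 20.0% | 0.0 |
| 0.20 | missing as smoking | 17.0% | 14.0% | +3.0 |

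With equal loss in the two arms, and the same q, every difference is zero. Imputing each arm's missing status at that arm's observed rate returns the complete-case result. Multiple imputation therefore repairs the q = 0.05 case only so far as recorded variables explain who relapsed.

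**6. Illustration of false-positive rate.** Exact enumeration of the pooled z test, 51 per arm, true abstinence equal in both arms at 15%, 20% or 30%, loss unrelated to smoking status, missing counted as smoking (a rule that the article does not state):

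| Missing EG / CG | Spurious difference (points) | One-sided rejection at 0.05 | Two-sided rejection at 0.05 |
|---|---|---|---|
| 20% / 20% | 0 | 0.049-0.051 | 0.048-0.051 |
| 10% / 20% | 1.5-3 | 0.076-0.099 | 0.054-0.065 |
| 10% / 30% | 3-6 | 0.117-0.178 | 0.072-0.110 |
| 10% / 40% | 4.5-9 | 0.175-0.293 | 0.107-0.193 |

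Steps 5 and 6 show what unequal loss would do. They do not show that it will occur.

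**The case against.** **Unequal loss is not in the text.** A reader might infer that EG participants who leave the programme stay reachable through the platform while CG leavers do not, so that outcomes are lost unequally by arm. The article does not support this. Section 2.3 describes remote monitoring for the duration of the programme, device use is voluntary, and the platform is itself the intervention, so a leaver may lose that channel too. The restriction to in-person visits in 2.4 governs monitoring by treating clinicians, not outcome collection. Section 2.1 has outcomes collected by standardised procedures by independent researchers, and 2.3 gives the same visit frequency in both arms. Moreover, if only a paper diary counts, platform contact alone supplies no endpoint either. This objection stands.

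**The status may be asked anyway.** Section 2.5.1 computes PPA from participants who report abstinence at the 6- and 12-month assessments, and Table 1 schedules smoking behaviour then. That could mean a question at the visit. But the next paragraph of 2.5.1 assigns both measures to the diary, so at best the text is unclear on its primary endpoint.

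**Missing data are addressed.** Imputation, sensitivity analyses and the acknowledged limitations soften the point. It would also be too strong to say that no analysis rule can help: complete-case analysis is unbiased in the q = 0.20 case above. What remains is that the right rule depends on an unknown quantity, and analysis cannot create outcomes that were never collected.

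**Detail may sit in the full protocol.** This is fair for the handling of non-attenders, and no weight is placed on its absence here. It does not cover the source that the article states or the contradiction about the diary.

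**Conclusion.** The point holds in a limited form. The article fixes a fragile sole source for both primary measures when a better one is available at visits that already take place in both arms. It also contradicts itself on whether the EG diary is kept by hand or by device, which is the best-documented way in which capture could differ between arms.

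Differential missingness is a credible risk and no more. The distortions calculated, -3.8 to +3.0 points in the first illustration and one-sided error of about 0.08 to 0.29 in the second, rest on assumed abstinence rates and assumed gaps in loss, and vanish when loss is equal. Counting missing as smoking is likewise an assumption.

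This should be corrected before enrolment, which section 2.7 says has not started. Confidence is moderate, because the full protocol is not shown.

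**What to change.** 1. In section 2.5.1 and Table 1, make the primary source one identical pair of questions: smoking status now, and any smoking since the last assessment. Ask them of every randomised participant at the existing 6- and 12-month visits in both arms, regardless of diary, device or programme use.
2. For non-attenders in either arm, obtain the same answers through the same scripted contact, and do not use the platform as an outcome channel for the EG alone.
3. State that stopping the diary, devices, platform or counselling is not withdrawal from follow-up.
4. Keep the diary as supporting data.
5. Reconcile the two statements in section 2.3 with sections 2.4 and 2.5.2, so that the diary is captured in the same way in both arms.

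The cost is protocol wording, two questions at visits already planned, and a short contact with non-attenders. The downside is that, where the diary is blank, CAR rests on recall over up to 6 months.
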